**Methods/Design:**

This study is a multicenter, randomized, double-blinded, parallel, and placebo-controlled trial that will last for 2 years. All qualified subjects with NOGDs and SQD will be included. The study population will be divided into the HGMX and placebo groups. To assess the efficacy of HGMX, we will mainly focus on changes in SQD symptoms scored by a Spleen Qi Deficiency Symptoms Grading and Quantifying Scale and evaluate changes in gastrin-17, the negative* Helicobacter pylori* conversion rate, body weight, body mass index, and gastroscopy findings. The safety of HGMX will be assessed by recording adverse events (AEs), severe AEs, treatment-related AEs and withdrawal due to AEs.

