#### 2.7.2. Secondary Outcomes

Changes in gastrin-17 (ng/L) levels in order to determine whether the intervention can improve gastric function were observedChanges in body weight (kg) and body mass index (kg/m^2^) were observedQuantitative changes were observed by gastroscopy

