### 2.10. Statistical Analysis

We will conduct an interim analysis at week 52 and a final analysis at week 104 with the help of the statistical software SPSS v23.0.

Specifically, an intention-to-treat analysis will be adopted for primary outcomes, while the per-protocol analysis will be performed as a sensitivity analysis. The last observation carried forward method will be used for missing data due to loss to follow-up. Continuous and categorical variables will be analyzed by t-test (or analysis of variance) and Pearson chi-squared test, respectively. In addition, continuous variables with a skewed distribution will be compared with the nonparametric rank-sum test. A P value ≤ 0.05 will indicate statistical significance for all the comparisons mentioned above, and group sequential method will be used to adjust the significant boundary for multiple t-test [19]. Subgroup analysis stratified by type of NOGDs (nonatrophic gastritis versus functional gastrointestinal disorders) and infection of* Helicobacter pylori* (yes versus no) will be performed. Furthermore, an analysis based on safety data set with no imputation will also be conducted. The incidence of AEs in the two groups will be compared using the Pearson chi-squared test, and all the AEs will be described in detail.

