The main purpose of this RCT is to clarify the long-term efficacy, safety, and compliance of HGMX, as a dietary TCM formula, in patients with SQD and NOGDs, with the guidance of TCM theory and evidence-based medicine methodology. The randomization of this RCT is standardly designed to minimize the selection bias and the period of follow-up is enough to observe the long-term efficacy and safety. Before the beginning of the trial, we appointed a training group contained senior methodologists, pharmacists, and physicians to conduct a standard operation procedure training in each research hospital. The diagnosis of TCM syndrome and the measurement of patient-reported outcomes will be performed by well-trained TCM physicians according to the standards to increase the consistency between difference investigators and hospitals. We also prespecified two sets of subgroup analysis based on expert's opinion and biological mechanism and used the group sequential method in repeated measures to reduce the probability of type I error. The results of the trial will be reported in strict accordance with the checklist of Consolidated Standards of Reporting Trials (CONSORT) Extension for Chinese Herbal Medicine Formulas. Therefore, this RCT can be expected to produce high-quality evidence.

This study may have some limitations. First, we will use an adjusted scale to assess SQD symptoms without reliability and validity tests, which could introduce a detection bias. We will conduct reliability and validity tests based on our study outcome data to test whether there exist any defects in reliability and validity. Second, because the placebo consists of early rice and oats and will be undertaken regularly according the study protocol, the patients in the placebo group may correct some bad diet habits during the participation, which may have positive effects on NOGDs and lead to bias in results (i.e., the estimate may tend to be conservative). Third, although we will take various measures to improve the patient compliance, the loss to follow-up is still probably inevitable during the long-term follow-up, resulting in attrition bias.

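### Section 2.10 lets every secondary efficacy outcome be called statistically significant at P ≤ 0.05; its only adjustment is for repeated t-tests, which leaves an 11–19% chance of at least one false secondary finding

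*Protocol article*

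**What the plan says.** Section 2.10 of the protocol article first names the tests: "Continuous and categorical variables will be analyzed by t-test (or analysis of variance) and Pearson chi-squared test, respectively", and "continuous variables with a skewed distribution will be compared with the nonparametric rank-sum test". It then sets the decision rule: "A P value ≤ 0.05 will indicate statistical significance for all the comparisons mentioned above". The same sentence goes on to say that a "group sequential method will be used to adjust the significant boundary for multiple t-test". The Discussion describes that device as having "used the group sequential method in repeated measures to reduce the probability of type I error".

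Section 2.7.1 names one primary outcome, the change in SQD score. Section 2.7.2 lists four secondary outcomes: gastrin-17, body weight, BMI and gastroscopy. The first is introduced as "Changes in gastrin-17 (ng/L) levels in order to determine whether the intervention can improve gastric function". The abstract says that, to assess efficacy, the trial will focus mainly on SQD symptoms and will also "evaluate changes in gastrin-17, the negative* Helicobacter pylori* conversion rate, body weight, body mass index, and gastroscopy findings".

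Section 2.10 schedules an interim analysis at week 52 and a final analysis at week 104. In Table 2, gastrin-17 is measured at baseline and at weeks 52 and 104, weight at every visit, and gastroscopy at baseline and week 104 only.

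**The concern.** The rule attaches the label of statistical significance to every comparison described before it, so it applies to four secondary efficacy outcomes as well as to the primary. The plan's one safeguard works along a different axis: a group sequential boundary controls the error from testing one outcome several times, not the error from testing several outcomes. Taken literally, it also stops at the t-test. A skewed gastrin-17 or weight variable would go to the rank-sum test, and a categorical outcome to the chi-squared test; neither is named in the adjustment.

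What is at stake is the wording of the conclusions. If the SQD comparison fails and one secondary outcome reaches 0.05, the published rule allows that outcome to be reported as a statistically significant difference between HGMX and placebo. A reader would take the error rate of such a claim to be 5%, whereas for the set of secondaries it is two to nearly four times that.

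**Working it through.** The article gives no family-wise error rate, so there is no stated figure to reproduce.

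**Inputs from the article**
- Threshold per comparison: 0.05 (section 2.10), taken as two-sided, critical value 1.96.
- Secondary outcomes: k = 4 (section 2.7.2).
- Time point: week 104, the one post-baseline visit at which Table 2 has all four measured.

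**Assumptions**
- The correlations between test statistics are not in the article and are varied below.
- HGMX has no effect on any of the four outcomes.

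**Step 1: independent tests.** Chance of at least one P ≤ 0.05 = 1 − (1 − 0.05)^4 = 1 − 0.8145 = 18.5%.

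**Step 2: common correlation ρ among the four.** Write each statistic as √ρ·U + √(1−ρ)·e, with U and e independent standard normal. Then the chance is 1 − E[{Φ((1.96 − √ρU)/√(1−ρ)) − Φ((−1.96 − √ρU)/√(1−ρ))}^4], the expectation being over U.

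| ρ | Chance of at least one false positive |
|---|---|
| 0 | 18.5% |
| 0.3 | 17.4% |
| 0.5 | 15.6% |
| 0.8 | 11.4% |

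**Step 3: overlap of weight and BMI.** With height nearly fixed, these two tests almost coincide (slightly less so in adolescents, since entry starts at age 14). Simulation with 1,000,000 draws of correlated normal statistics gives:
- weight–BMI correlation 0.90 to 0.99, other outcomes independent: 16.1% down to 14.8%;
- weight–BMI correlation 0.95, other correlations 0.5: 13.7%.

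So about 14–16%. As a cross-check, dropping BMI leaves three tests: 1 − 0.95^3 = 14.3% if independent, and about 12.5% from the step 2 formula with k = 3 and ρ = 0.5.

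**Step 4: does the group sequential boundary change this?** Suppose it is applied to every secondary outcome and works exactly. Each outcome then has a 5% error over all its looks. Four such outcomes, if independent, again give 1 − 0.95^4 = 18.5%. The boundary holds each outcome to 5% but does nothing about there being four.

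**Step 5: the literal gap in the boundary.** If one outcome were tested by rank-sum at both weeks 52 and 104, each at an unadjusted 0.05, with correlation 0.5 between the two statistics, the chance of a false positive on that outcome alone would be about 9%. This holds only if the secondary is tested at the interim, which the article does not state, and if the word t-test is read strictly.

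**The case against.** **The outcomes are already ranked.** There is one primary outcome, the sample size rests on it, the others are headed as secondary, and the abstract puts the main focus on SQD symptoms. This stands. A reader might infer that the trial's overall type I error is inflated, or that the plan has no hierarchy at all. The article does not support that: however many secondaries are tested, the primary test's error rate is unaffected. Nor does the article say that a significant secondary would establish efficacy if the primary fails. The harm depends on how a secondary result is reported.

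**Ordering and labelling belong in an analysis plan that is not shown.** This stands for anything merely absent, so a missing testing order is not the point here. The point is a rule that is stated: 0.05 means significance for all the listed comparisons. An analysis plan that gated the secondaries or made them exploratory would have to depart from that sentence.

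**The sentence continues with an adjustment, and gastrin-17, weight and BMI are continuous.** This also stands, and it rules out a stronger reading. A reader might test the secondaries at weeks 52 and 104 without adjustment and arrive at 20% or more. That ignores the stated boundary wherever a t-test is used. The week-104 figures do not depend on it, as step 4 shows.

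**H. pylori conversion should not enlarge the family.** Agreed. It is in the abstract but not in section 2.7.2, and that inconsistency is a separate matter. It is not counted here.

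**The remaining texts can be over-read.** The gastrin-17 phrase may only explain why it is measured, and the Discussion claims lower type I error for repeated measures, not across endpoints. Both are fair. The point does not need either text, because the significance rule and the abstract's efficacy list carry it.

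**Conclusion.** The point holds in a limited form. As written, section 2.10 allows any of four secondary efficacy outcomes to be declared statistically significant at 0.05, and its only adjustment does not address the number of endpoints. Under no effect, the chance of at least one such declaration at week 104 is about 11–19% for common correlations between 0.8 and 0, and about 14–16% allowing for the weight–BMI overlap. These figures rest on assumed correlations, two-sided tests and a count of four outcomes; none is given in the article as an error rate. Even the lowest is more than twice 5%. The primary SQD comparison is not affected by the number of secondaries. The consequence is for what may be claimed from the secondary results, which justifies a change of wording but not of design.

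**What to change.** In section 2.10:

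- Limit the P ≤ 0.05 significance claim to the primary SQD comparison.
- Report the secondary outcomes as supportive or exploratory, with estimates and 95% confidence intervals and no significance claim. If claims are wanted, test them only after a significant primary result, either by Holm (first threshold 0.05/4 = 0.0125 for four outcomes, or 0.05/3 = 0.0167 if BMI is not tested) or in a sequence fixed before unblinding. The article gives no ground for one particular order, so the sponsor should choose it.
- Present BMI as a re-expression of body weight, not as a separate test.
- Word the group sequential adjustment so that it covers whichever test is used at weeks 52 and 104, including rank-sum and chi-squared, and state which outcomes it applies to.

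This costs a few sentences and no additional patients, visits or data. The downside is that a nominally significant secondary result can no longer be claimed as an effect on its own.

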## 2. Methods/Design

### 2.1. Trial Design

This study is a multicenter, randomized, double-blinded, parallel-group, placebo-controlled trial that aims to determine whether HGMX is an effective and safe treatment for improving the symptoms of SQD in patients with NOGDs. The study population will be randomly divided into the HGMX group and the placebo group. The overall design is presented in Figure 1. The trial has been registered at Clinicaltrials.gov (No. NCT03019042). In order to guarantee standardized processes, precise judgment, and the safety of all participants, our study will be performed in accordance with the principles of Good Clinical Practices and the Declaration of Helsinki. We designed and reported our protocol according to Standard Protocol Items: Recommendations for Interventional Trials. [16].

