### 2.9. Sample Size Estimation

This RCT is a superiority study. From an overall consideration, we will restrict the type I error (*α*) and type II error (*β*) to 0.05 and 0.2, respectively. The variation between groups and the combined standard deviation of the primary outcome were estimated at 6.0 and 13.0, respectively, based on the results of a preliminary observational study. In addition, a maximum rate of 20% withdrawal or loss to follow-up was adopted. Therefore, with the corresponding sample size estimation equation [18] and the consideration of funding constraints, we computed an expected sample size of 200, with 100 in each group.

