## 3. Discussion

Since the 20th century, the disease spectrum has undergone significant changes: the chronic diseases, such as nonorganic disorders, diabetes mellitus, cardiovascular diseases, and cancer, become the major disease burden. The development of these diseases is multifactorial and the diet often plays an important role. Thus, diet-related management (e.g., diet control and nutrition supplement) could be a treatment approach for these diseases. However, the clinical nutriology simply based on adjustment of diet structure has limitations on the efficacy.

Using the TCM theory, the food (including herbs in the list of food) can be made into dietary TCM formula, which can be daily eaten and has treatment effects for chronic diseases. HGMX is a dietary TCM formula developed based on this concept. After screening of a large number of classic TCM formula, Shen Ling Bai Zhu San was chosen as the basic formula of HGMX, because its efficacy and safety for gastrointestinal diseases are validated by thousands of years of application and animal and clinical researches. On the other hand, except for atractylodes, all components of Shen Ling Bai Zhu San are in the official list of food designated by the Ministry of Health of China. Thus, it can be easily modified to a pure dietary formula on the premise without changing the main effects. During the two years of marketing, no adverse events related to HGMX are reported. Therefore, the safety of this RCT can also be guaranteed.

To validate the potential effects of HGMX on gastrointestinal protection and systemic symptom improvement, we intend to perform a series of RCTs. The study series contains 3 RCTs, with the other two focusing on patients with peptic ulcers (NCT03320538) and on patients who underwent radical gastrectomy for gastric cancer (NCT03025152). These RCTs are also corresponding to three main applications of dietary TCM formula: (1) use for the treatment of nonorganic disorders; (2) adjuvant therapy for the treatment of chronic diseases; and (3) adjuvant therapy for the rehabilitation of major diseases.

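### Safety is a stated aim, but the only between-group safety method is a Pearson chi-squared test, which at 100 per arm cannot support a safety conclusion for uncommon events; report risk differences with 95% confidence intervals

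*Protocol article*

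**What the plan says.** The protocol article treats safety as an aim in the abstract's objectives, in section 2.1 (the trial "aims to determine whether HGMX is an effective and safe treatment") and in the Discussion's statement of the main purpose.

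Section 2.7.3 lists four safety outcomes: adverse events (AEs), serious events (SAEs), treatment-related AEs and withdrawal due to AEs. The AE definition is broad. It covers ECG and laboratory abnormalities as well as events seen by doctors or reported by patients, and follow-up lasts two years.

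On analysis, section 2.10 says: "The incidence of AEs in the two groups will be compared using the Pearson chi-squared test", and the same sentence adds a detailed description of every AE. It also says that "an analysis based on safety data set with no imputation will also be conducted". The only threshold in that section is "A P value ≤ 0.05 will indicate statistical significance for all the comparisons mentioned above". That sentence comes before the AE sentence, so applying it to AEs is the natural reading but is not explicit.

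Section 2.9 derives the size from a difference of 6.0 and a standard deviation of 13.0 on the primary outcome, in a superiority design: "we computed an expected sample size of 200, with 100 in each group". It uses no event rate and no safety margin.

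**The concern.** A chi-squared test of equal incidence can flag harm, but it cannot show that harm is small. If it does not reject, the reader learns only that the data are compatible with no difference, and not how large an excess they are also compatible with. At a sample size chosen for a continuous symptom score, that excess can be large when events are uncommon.

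The product is already marketed and is meant for daily long-term intake, so this trial's safety statement is likely to be relied on. With a test as the only comparison named, the trial would have no stated way of saying what excess of events it has ruled out.

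**Working it through.** **1. The plan's own figure.** With two-sided α = 0.05 and power 0.80, n per arm = 2 × (1.960 + 0.842)² × (13/6)² = 73.7, so 74. Allowing for 20% loss, 74/0.8 = 92.5, so 93 per arm. The stated 100 per arm is above this, so the trial is not undersized for its primary outcome. No term in the calculation concerns safety.

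**2. Inputs for the safety check.** From section 2.9: n = 100 per arm, or 80 per arm if the planned 20% loss is removed. From section 2.10: Pearson test, P ≤ 0.05. The control AE rate is not given in the documents, so it is an assumption, shown as a range.

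**3. Power for a doubling.** For every pair of counts (x₁, x₂) from independent binomials, compute the uncorrected Pearson statistic, X² = (p̂₁ − p̂₂)² / [p̄(1 − p̄)(2/n)], where p̄ is the pooled proportion. Then sum the probabilities of all pairs with X² ≥ 3.841.

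| Assumed rates | Power, 100 per arm | Power, 80 per arm |
|---|---|---|
| 2% vs 4% | 11% | 10% |
| 5% vs 10% | 27% | 21% |
| 10% vs 20% | 52% | 42% |
| 15% vs 30% | 73% | 63% |
| 20% vs 40% | 88% | 80% |
| 30% vs 60% | 99% | 97% |

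Power for a doubling passes 50% at a control rate of about 10% with 100 per arm, and about 12% with 80.

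**4. Smaller excesses at common rates.** The same calculation at 100 per arm (80 in brackets) gives 37% (31%) for 20% vs 30% and 59% (50%) for 30% vs 45%.

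**5. What a non-significant result would leave open.** Suppose 10/100 on HGMX and 5/100 on placebo. The pooled proportion is 15/200 = 0.075, and X² = 0.05² / (0.075 × 0.925 × 0.02) = 1.80, so P = 0.18. The Wilson 95% limits are 5.5% to 17.4% for 10/100 and 2.2% to 11.2% for 5/100. Newcombe's interval for the difference combines them:

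- lower: 0.05 − √[(0.100 − 0.055)² + (0.112 − 0.050)²] = −0.026
- upper: 0.05 + √[(0.174 − 0.100)² + (0.050 − 0.022)²] = +0.130

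(The limits were computed unrounded.) The test would not reject, yet an excess of 13 percentage points would remain compatible with the data.

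**6. What the interval could show.** With 5/100 in each arm the Newcombe interval is −6.8 to +6.8 points, so the trial could then say it had excluded an excess above about 7 points. The chi-squared test (X² = 0, P = 1) could not say that.

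**The case against.** Several points on the other side stand.

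- **Power depends on a rate the documents do not give.** A reader might infer that a doubling of AEs would usually be missed whatever the rate. The table does not support that. AEs are broadly defined and collected for two years, so overall incidence could well exceed 10%, and from about 20% a doubling is detected with roughly 80% power or more.
- **No rule equates non-significance with safety.** A reader might infer that the authors will report a non-significant test as proof of safety, and point to the Discussion: "no adverse events related to HGMX are reported. Therefore, the safety of this RCT can also be guaranteed". That sentence argues from marketing experience about the safety of running the trial. It does not interpret the section 2.10 test.
- **The test is not the whole safety assessment.** All AEs will be described in detail, treatment-related AEs have case-level criteria in 2.7.3, and a safety-set analysis is planned. These have value, but none of them, as stated, quantifies a between-group difference.
- **80 per arm is pessimistic.** Participants who leave can still contribute events up to that time, so the 100-per-arm column is the fairer one for safety.
- **Sizing on the primary outcome is ordinary**, and interval estimates may appear in an analysis plan that is not shown. But the article does name a method for this aim, and the criticism is of that choice.

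Sparse counts might also suggest a switch to Fisher's exact test. That would not help. With a true rate of 1% in both arms and 100 per arm, the Pearson test already rejects only 1.4% of the time, and Fisher's test is more conservative still.

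**Conclusion.** The point holds within limits. The one between-group safety method stated does not match the aim it serves when events are uncommon. If the control rate is below about 10%, the test has roughly 50% power or less to detect a doubling with 100 per arm, and a non-significant result could not support a safety conclusion. SAEs, treatment-related AEs and withdrawals due to AEs may fall in that range. Overall AE incidence may not.

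This rests on assumed event rates, on reading the 0.05 threshold as applying to AEs, and on the uncorrected two-sided test. It does not show that the sample size is wrong or that the authors will misread the result. It shows that a better summary is available at almost no cost, and it is worth adopting.

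**What to change.** In section 2.10, replace the AE comparison with wording such as: *For each safety outcome in 2.7.3 (participants with at least one AE, SAE, treatment-related AE, or withdrawal due to an AE) we will report the number and percentage per arm and the risk difference with a two-sided 95% confidence interval (Newcombe) as the main safety result. The chi-squared P value will be supplementary. The trial is not powered for safety comparisons, and a non-significant difference will not be taken as evidence of safety.* Keep the detailed description of all AEs.

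This needs no extra participants, visits or data. The downside is a more cautious safety conclusion.

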### 2.6. Interventions

Our participants are grouped into the HGMX group (experimental group) and the control group. In the HGMX group, participants will be treated with an oral dose of 30 g/day HGMX. Every 30 g of HGMX contains 10.1 g of herbal material (detailed components of HGMX are shown in Table 1) and 19.9g early rice and oats. Participants in the control group will receive the same dose of placebo, which consists of 66.7% early rice and 33.3% oats with the same preparation, packaging, labeling, and appearance but a slightly different taste and smell than the real HGMX. All subjects will be treated for a duration of 2 years (104 weeks). During follow-up, patients can be treated as necessary based on clinical guidelines for acute and chronic diseases (such as hypertension, diabetes, and osteoarthritis) that are not included in the exclusion criteria.

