#### 2.7.3. Safety Outcomes

Incidence of adverse events (AEs), including abnormal ECG and dramatic changes (indicated by a value outside 2 × the lower or upper normal reference interval) in alanine transaminase (U/L), aspartate aminotransferase (U/L), total bilirubin (*μ*mol/L), direct bilirubin (*μ*mol/L), indirect bilirubin (*μ*mol/L), or serum creatinine (*μ*mol/L). In addition, doctor-observed and patient-reported AEs are also included.SAEs are those AEs that could result in treatment in the hospital, a longer in-hospital stay, transfer to an intensive care unit, disability, life-threatening complications, and death.Treatment-related AEs defined as those AEs fully meet the following condition [17]: (1) the occurrence time is logically related to treatment administration; (2) the adverse effects cannot be interpreted by cointerventions and comorbidities; (3) the adverse effects should relieve or disappear when the treatment is withdrawn; (4) the relation is supported by definitively pharmacological or phenomenological mechanism.Withdrawal was due to AEs.

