### 2.8. Study Follow-Up and Outcome Assessments

The durations of follow-up and treatment are equal at 2 years. In our study, all participants will be evaluated 8 times: at baseline and in weeks 2, 4, 8, 26, 52, 78, and 104. After the qualified participants sign the informed consent form, they will document the characteristics of their own symptoms in the baseline case report form (CRF) and then record the baseline (first visit) physical and laboratory examination data. In weeks 2 and 4, participants will complete the Spleen Qi Deficiency Symptoms Grading and Quantifying Scale (SQD scale) and a physical examination. In weeks 8, 26, 52, 78, and 104, an ECG and laboratory examination, including routine blood, urine, and stool tests, are required. Gastrin-17 and* Helicobacter pylori* will be assessed at both weeks 52 and 104. Gastroscopy will be performed at only baseline and the last visit.  Table 2 provides an overview of the study procedures.

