### 2.13. Discontinuation and Withdrawal

After the assessment of previous compliance, study of the corresponding participant will be discontinued for the following reasons, and the participant will be withdrawn without laboratory examination.The symptoms of SQD worsen and the patient must be treated with an alternative regimen to improve his/her statusThe SAEs occurred. All SAEs will be reported by our principle investigators to the ethics committee of the local hospital and the Jiangxi Food and Drug Administration Agency within 24 hours. Several emergency measures will be taken to minimize the harm to patients when a SAE occurred. We will immediately assign senior doctors to implement rescue measures according to the corresponding guidelines. If acute toxicity caused by overdose is determined, the doctors will give measures to accelerate the drug excretion, and, if necessary, the intensive care (e.g., electrocardiograph monitoring and assisted respiration) will be performed until patients' vital signs are stable. If the patient is unable to come to the research hospital, we will advise him/her to visit the local hospital and give consultation with the local doctors, and, if necessary, we will appoint senior doctors to the local hospitalThe patient decides to take prohibited drugs to improve NOGDsPoor compliance includes an intake dose less than 80% of that required or two follow-ups beyond the specific deviation rangeParticipant has personal concerns

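### The only stated between-arm AE test ignores time on study; a prespecified time-to-first-AE analysis would be a cheap supplement, since unequal withdrawal would bias crude incidence modestly

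*Protocol article*

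**What the plan says.** The safety comparison in section 2.10 (Statistical Analysis) is one sentence: "The incidence of AEs in the two groups will be compared using the Pearson chi-squared test". The same section adds that every AE will be described and that the safety set is analysed without imputation. It names no analysis of AEs that uses time on study.

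Treatment and follow-up both last 104 weeks (2.6, 2.8). Section 2.9 allows for early exits: "a maximum rate of 20% withdrawal or loss to follow-up was adopted". Section 2.13 lists what ends participation: "The symptoms of SQD worsen and the patient must be treated with an alternative regimen", an SAE, use of prohibited drugs, poor compliance (intake under 80%, or two follow-ups outside the window) and personal concerns. On these grounds "study of the corresponding participant will be discontinued for the following reasons, and the participant will be withdrawn without laboratory examination".

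Section 2.7.3 counts ECG abnormalities and marked laboratory changes as AEs, and "doctor-observed and patient-reported AEs are also included". It makes withdrawal due to AEs a separate safety outcome. It does not say whether worsening of the SQD symptoms is an AE. Table 2 schedules AE recording at weeks 8, 26, 52, 78 and 104, the same visits as the ECG and laboratory tests.

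**The concern.** A crude proportion is a fair comparison when both arms are watched for about the same time. Here several exit rules depend on efficacy or tolerability. The rules are the same in both arms, but how often they apply need not be. If the product works, placebo participants may leave more often for worsening or prohibited drugs. If it is poorly tolerated, its own participants may fall below the intake threshold more often.

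The exits that matter are those with no AE recorded: worsening, prohibited drugs, poor compliance and personal reasons. A participant who leaves because of an SAE is already an event in the crude count and does not create this bias.

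Safety is part of the stated aim (2.1), and the Discussion stresses the long term. If AE-free exits differ by arm, crude incidence can differ between arms of equal true risk, or a true difference can be diluted. The one stated test cannot separate this from a real effect.

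**Working it through.** **Inputs from the article.** 100 per arm and at most 20% withdrawal (2.9); 104 weeks (2.6, 2.8); significance threshold 0.05 (2.10), taken as two-sided. The article gives no figure for the AE comparison, so there is none to reproduce.

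**Assumed, not in the article.** A constant AE hazard λ of 0.1, 0.3 or 0.5 per year, equal in both arms; withdrawal w of 15% v 25% (20% overall); exits spread evenly over 104 weeks, or all within 26 weeks.

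**Step 1. Two-year risk if fully observed.** F = 1 − exp(−2λ) = 0.181, 0.451, 0.632.

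**Step 2. Mean risk up to exit for a leaver,** with exits uniform over T years. m = 1 − [1 − exp(−λT)]/(λT). For T = 2: 0.094, 0.248, 0.368. For T = 0.5: 0.025, 0.071, 0.115.

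**Step 3. Crude incidence** = (1 − w)F + w·m. Example, λ = 0.3, even exits: 0.85 × 0.451 + 0.15 × 0.248 = 0.421, against 0.75 × 0.451 + 0.25 × 0.248 = 0.400. The chi-squared rejection probability comes from exact binomial enumeration with 100 per arm. The ratio is the arm with 15% withdrawal over the arm with 25%.

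| Exits | λ | 15% arm | 25% arm | Ratio | Rejection |
|---|---|---|---|---|---|
| Even | 0.1 | 0.168 | 0.159 | 1.055 | 5.4% |
| Even | 0.3 | 0.421 | 0.400 | 1.051 | 6.2% |
| Even | 0.5 | 0.592 | 0.566 | 1.047 | 7.0% |
| Within 26 weeks | 0.1 | 0.158 | 0.142 | 1.110 | 6.2% |
| Within 26 weeks | 0.3 | 0.394 | 0.356 | 1.107 | 8.6% |
| Within 26 weeks | 0.5 | 0.555 | 0.503 | 1.103 | 12.3% |

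Withdrawal of 10% v 20% gives almost the same: ratio 1.05 and 5.4% to 6.9% if even, 1.10 to 1.11 and 6.2% to 12.1% if early. Equal withdrawal of 20% gives ratio 1.00 and 5.0% to 5.6%, which is the test's own level.

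**Step 4. Direction.** Suppose the 10 extra leavers per 100 go for worsening, and a share s of them have it recorded as an AE. Their average contribution becomes s + (1 − s)m, which equals F when s = (F − m)/(1 − m). The bias therefore cancels at s = 0.10, 0.27, 0.42 (even) or 0.16, 0.41, 0.58 (early). If all have it recorded, the ratio is 0.67, 0.89, 0.94 (even) or 0.66, 0.88, 0.94 (early).

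**Step 5. Does time to first AE help?** In simulation at 15% v 25% with onset dates, the log-rank test rejected in 4.5% to 5.5% of trials, with a hazard ratio of 0.99 to 1.01. This covered constant hazards and hazards 3 or 5 times higher in the first 26 weeks. A person-year rate ratio was unbiased under constant hazards, but with that clustering it fell to 0.97 to 0.99 and its test rejected in up to 11.1%. That is the reason to prefer time to first AE.

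**The case against.** The strongest reply is that nothing here is an error. A chi-squared test on AE incidence is conventional, the AEs will also be described, and supplementary safety displays are often left to an analysis plan that is not shown. Every withdrawal split and AE rate above is assumed. The crude gap with even exits is 0.9 to 2.6 points, about one to three participants per 100. The 12.3% needs the imbalance, wholly early exits and the highest hazard together. The article also reports withdrawal due to AEs separately and concedes that "the loss to follow-up is still probably inevitable during the long-term follow-up, resulting in attrition bias".

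Most of this stands, and it keeps the point minor. It does not remove it. The article names a method for this comparison, that method disregards time on study, and a method that uses it needs only AE data the trial already plans to record. Reporting withdrawals due to AEs shows AE-driven exits but not the AE-free ones that cause the bias, and naming attrition as a limitation does not adjust for it.

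A reader might infer more: that the chi-squared test is invalid and should be replaced, or that it is known to favour one arm. The documents support neither. They give no withdrawal by arm, the bias is nil when withdrawal is equal, and its sign depends on how worsening is recorded. That 2.7.3 does not settle this is a matter of definition an article may leave to the full protocol, and is not raised as a fault.

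**Conclusion.** The point holds as a minor, conditional weakness. The one stated between-arm AE test is unaffected by equal withdrawal. Under a 10-point imbalance around the 20% planning maximum, and equal true AE hazards of 0.1 to 0.5 per year, it is biased by about 5% in ratio when exits are evenly spread and about 10% when all are early. False positives rise from about 5% to at most 7.0% and 12.3% respectively. These sizes rest on constant hazards, the assumed splits and exit times, and leavers without an AE staying in the safety set as non-events. The direction is open. This supports a supplement to the planned analysis and not its replacement.

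**What to change.** Keep the chi-squared test and the AE description in 2.10, and add one prespecified supplementary analysis, for example:

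*Time to first AE will be compared between arms with Kaplan-Meier curves, a log-rank test and a hazard ratio with 95% confidence interval. Participants without an AE will be censored at their last AE assessment. Onset dates will be used where available, otherwise the visit at which the AE was recorded. Person-years of observation and withdrawals by reason will be reported by arm.*

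This analysis should be done whatever the data look like. A rule that picks between person-year rates and time to event according to observed clustering would invite a data-driven choice.

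**Cost.** One paragraph of analysis wording and a few table columns, with slightly more analysis work; no new participants, visits or staff.

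**Limits.** Timing is coarse if only visit dates exist, because scheduled AE recording starts at week 8. Exits before then have no scheduled AE record: 8/104 = 8% of leavers if exits are even, 8/26 = 31% if all fall within 26 weeks. Leavers also have no exit laboratory examination, which this does not repair. The analysis assumes that withdrawal is unrelated to later AE risk, which exits for worsening may break, so it reduces the bias and does not remove it.
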